**2.4 STATISTICAL APPROACH**

**2.4.1 Sample Size and Power**

This is an exploratory observational trial to demonstrate feasibility and the statistical power analysis for the sample size is not appropriate. The sample size of 10 for this clinical trial is based upon: 1) exposing a minimum number of patients to potential risks of the experimental treatment while still obtaining useful information; 2) the intent to collect detailed and comprehensive data in each subject to provide comprehensive information relevant for design of a future larger trial, and also provide adequate specimens for the Ancillary Studies. This is an exploratory Phase I/II clinical trial focused on establishing proof-of-concept, and providing access to a novel treatment regimen in patients with a very high risk of hospital mortality.

Given the nature of this initial, exploratory and uncontrolled clinical trial, definitive power calculations are speculative. Nonetheless, high efficacy of the experimental treatment (as we anticipate) could produce evidence of same, given the usual high mortality of historical control patients. We are planning a study with 10 experimental subjects and 100 historical control subjects. A conservative estimate of survival among historical controls is 50%. If our treatment results in 90% survival, we will be able to reject the null hypothesis that the failure rates for experimental and control subjects are equal with probability (power) 0.6.

**2.4.2 Statistical Analysis**

The data analysis for the primary aim begins by describing the sociodemographic, and medical characteristics of the population at baseline. Descriptive statistics, including measures of central tendency and dispersion, will be computed for continuous data (e.g., age). Frequency distributions will be estimated for categorical data (e.g., gender). Mixed effects regression models will be used to assess the treatment effects on gas exchange. Main effects will include treatment, intubation status, time, as well as a treatment by time interaction and random effects for slope and intercept. Additional main effects may include those baseline characteristics not balanced by random assignment, if any are identified. A linear regression model will be used to assess the effect of treatment on the number of ventilation-free days. As with the mixed effects model, main effects will include treatment, intubation status and characteristics not balanced by random assignment, if any are identified. For both the mixed effects model and the linear regression model, the model assumptions (e.g., normality of residuals) will be investigated. If the assumptions are violated, transformations will be investigated. If adequate transformations cannot be identified, nonparametric approaches will be utilized.

Treatment-emergent adverse events are defined as any new event reported after enrollment, or any event that is worse in severity than at any time during the baseline period. Intergroup differences in percentages of treatment-emergent adverse events will be assessed using Fisher's exact test or chi-square test.

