**SECTION 2 – RESEARCH DESIGN AND METHODS**

**2.1 CLASSIFICATION AND METHODOLOGICAL DESIGN**

This is a prospective, open-label Phase II, non-randomized clinical trial to assess the feasibility and safety of combined plasma exchange (PEX), rituximab, and conventional corticosteroid administration in patients with acute IPF exacerbations.

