**2.2 DETAILED DESCRIPTION OF RESEARCH ACTIVITIES**

**2.2.1 Study Design and Procedures**

The proposed combined treatment of plasma exchange (PEX), rituximab, and corticosteroids is routinely provided for a specific subset of patients with a unique form of autoimmune interstitial lung disease, called anti-synthetase syndrome or anti Jo-1 antibody syndrome at UPMC PUH. In this proposal, we plan to extend this treatment to the more general IPF exacerbation patient population which currently is most commonly treated with high dose corticosteroids or pulse solumedrol alone. All clinical and laboratory testing will be considered part of routine medical care for patients with no therapeutic options and a very high recognized mortality rate. In addition to routine medical care, specific T-cell and B-cell assays will be conducted in the laboratory of a Co-PI ([name]).

After hospital admission for acute IPF exacerbation (and after informed consent is obtained), subjects will receive the standard steroid treatment followed by initiation of the PEX and rituximab regimens. These latter two agents will require insertion of a dialysis/apheresis catheter into a central vein.

Standard Steroid Treatment: One gm of methylprednisolone i.v., on day 0, followed by 40 mg/day i.v. on days 1-4, and days 6-12 (or the p.o. prednisone equivalent). Methylprednisolone 100 mg i.v. will be administered on days 5 and 13. Steroid doses will then be 20 mg methylprednisolone i.v. (or p.o. prednisone equivalent) from days 14-28, and then reduced thereafter at the discretion of the principle investigator at each site. There are no published data that show efficacy of this agent at these doses. Nonetheless, steroid treatments (with highly varied doses and durations) are currently the standard of care for IPF patients with acute exacerbations.4 The high initial dose is intended to optimize early lympholysis. Administration of methylprednisolone 100 mg i.v. on days 5 and 13 will standardize steroid treatments among the two trial arms, as these agents are recommended prior to rituximab infusions.78 Steroid doses < 20 mg methylprednisolone i.v. (or p.o. prednisone equivalent) from days 14-28 are important to establish as this dose is an appropriate cutoff for consideration of lung transplantation.

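### Section 2.4.2 prescribes a two-arm randomised analysis, but all 10 enrolled patients receive one regimen, so its treatment terms cannot be identified among them

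*Protocol*

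**What the plan says.** The design sections describe one treated group. Section 2.1 states: "This is a prospective, open-label Phase II, non-randomized clinical trial". Section 2.4.1 calls the trial uncontrolled: "Given the nature of this initial, exploratory and uncontrolled clinical trial, definitive power calculations are speculative". The treatment table in 2.2.1 shows a single combined regimen, and 10 patients are to be enrolled.

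The analysis section describes two groups. For gas exchange, 2.4.2 says: "Main effects will include treatment, intubation status, time, as well as a treatment by time interaction and random effects for slope and intercept". On covariates: "Additional main effects may include those baseline characteristics not balanced by random assignment, if any are identified"; the same appeal to randomisation is repeated for the second model. That second model is: "A linear regression model will be used to assess the effect of treatment on the number of ventilation-free days". On safety: "Intergroup differences in percentages of treatment-emergent adverse events will be assessed", by Fisher's exact or chi-square test. Section 2.2.1 also says that the steroid schedule "will standardize steroid treatments among the two trial arms".

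Historical controls appear in 2.3.2 as the comparator for the secondary composite (alive at 60 days, or alive to transplantation), and in 2.4.1 as the 100 controls behind the power statement. Neither 2.3.1 nor 2.4.2 names a comparator for PaO2, ventilation-free days or adverse events.

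**The concern.** Section 2.3.1 makes feasibility and safety the primary outcomes, with PaO2 and haemodynamic deterioration as safety measures. Section 2.4.2 introduces its models as the analysis for the primary aim. If every analysed patient is treated, a treatment coefficient has nothing to be contrasted with.

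An analyst who follows the text must either drop terms after seeing the data or improvise a comparator. The first departs from the plan without a rule. The second could lead to a change over time in sick inpatients, or a difference between eras of care, being reported as a treatment effect on gas exchange or safety.

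**Working it through.** **Inputs.** Treated patients: 10 (2.4.1). Concurrent controls: none (2.1, 2.4.1). PaO2 days: 0, 3, 5, 7, 14 and 28 while in hospital (2.3.1); the visit schedule in 2.2.2 lists only days 0, 7, 14 and 28. The result below is the same on either set of days.

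**The plan's own figure.** Section 2.4.2 gives none. The only power figure, 0.6 in 2.4.1, belongs to the secondary survival comparison, 90% of 10 against 50% of 100. Alpha and sidedness are not stated; I assume two-sided 0.05. With a continuity correction:
- corrected difference: 0.40 − 0.5 × (1/10 + 1/100) = 0.345
- pooled proportion: (9 + 50)/110 = 0.536; null standard error √(0.536 × 0.464 × 0.11) = 0.165
- alternative standard error: √(0.09/10 + 0.25/100) = 0.107
- power: Φ[(0.345 − 1.96 × 0.1654)/0.1072] = Φ(0.194) = 0.577

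That agrees with 0.6 at the one decimal given. Methods without the correction give more (pooled z 0.760). This point does not rest on the figure. It shows only where the historical controls enter the plan.

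**Mixed model.** For patient i at time t, with treatment T, intubation U, random intercept a and random slope b:

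PaO2 = β0 + β1·T + β2·U + β3·t + β4·T·t + a + b·t + error

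With T = 1 for all 10 patients:

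PaO2 = (β0 + β1) + β2·U + (β3 + β4)·t + a + b·t + error

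- The treatment column equals the intercept column, and treatment × time equals time.
- Fixed-effect columns: 5. Rank: 3, computed for 10 patients at six days with both intubation states present.
- Only the sums β0 + β1 and β3 + β4 can be estimated, so β1 and β4 cannot. The mean-zero random effects do not change this.
- The same layout with a hypothetical second arm of 10 has rank 5 of 5, so the missing group is the cause.

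**Ventilation-free days.** The columns are intercept, treatment and intubation: 3 columns, rank 2. The treatment coefficient is not estimable.

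**Adverse events.** With one group, the 2 × 2 table has rows (x, 10 − x) and (0, 0). The odds ratio is undefined. Fisher's p is 1 for any x, because only one table is possible given the margins.

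**What 10 patients do support.** Exact (Clopper–Pearson) two-sided 95% intervals:
- 0/10: 0 to 1 − 0.025^(1/10) = 0.308, so 0 to 31%
- 1/10: 0.3 to 44.5%
- 3/10: 6.7 to 65.2%

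**The case against.** The strongest reply is that the rank result assumes that the 10 patients are the whole dataset. Section 2.4.1 plans 10 experimental and 100 historical control subjects, so the treatment and intergroup terms might be read as experimental against historical. This stands in part: if historical controls supplied the same variables, the terms would be algebraically estimable. But the protocol does not assign the controls to these outcomes or say what their records contain. I assume, and cannot show, that they are unlikely to hold PaO2 after more than 20 minutes on 100% FiO2 on fixed days. For ventilation-free days and adverse events the protocol gives no basis either way. Even with the data, the contrast would be non-randomised and the references to random assignment would still be wrong.

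A second reply is that the trial is exploratory and that detail belongs in an analysis plan. No go/no-go rule in the protocol depends on these models, which limits the harm. But this is not missing detail. The protocol states a specific analysis that does not fit its design, and an analysis plan that followed it would inherit the mismatch.

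A reader might also infer three stronger things that the document does not support:
- **That the primary aim cannot be analysed at all.** Baseline description, event percentages, the time trend and possibly the intubation effect can all be produced.
- **That ventilation-free days is certainly outside the endpoints.** It is not among those shown, but 2.3.1 announces three safety variables and the text at hand shows two. The third may have been left out or lost when the file was read.
- **That a random slope is wrong here.** With 10 patients it may fit poorly, but no calculation shows this. Section 2.4.2 already provides for assumption checks and fallbacks, so the choice is a preference.

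Finally, a single-arm model does not separate treatment from natural course either. That is correct, and it is why its output must be labelled a time course.

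**Conclusion.** The point holds: 2.4.2 is wrong as written for this design. None of its three treatment contrasts (gas exchange, ventilation-free days, adverse events) can be estimated from the 10 enrolled patients. The mixed model has rank 3 of 5, the ventilation-free-days model rank 2 of 3, and the intergroup test has one group. The randomisation wording in 2.4.2 and the two-arm wording in 2.2.1 contradict 2.1 and 2.4.1 whatever comparator is used.

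The rank figures assume that the analysed data are the 10 treated patients and that both intubation states occur. If only one state occurs, the intubation effect is lost as well. The conclusion does not depend on the 0.6 power figure, the number of PaO2 days or the random-effects structure.

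**What to change.** Amend the text as follows.
1. In 2.4.2, remove the treatment and treatment-by-time terms, the intergroup test and both references to random assignment. In 2.2.1, remove the reference to two arms.
2. Analyse PaO2 as within-patient change from day 0 by study day, adjusted for intubation status. Call it a time course, not a treatment effect. Because PaO2 is recorded only in hospital, give the number of patients contributing on each day.
3. Report adverse events and each deterioration variable as number and percent of patients with exact two-sided 95% intervals.
4. Report ventilation-free days descriptively and reconcile it with 2.3.1, so that the number of variables announced matches the number listed.
5. Keep the historical-control comparison for the survival composite only.

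The cost is protocol wording (and analysis-plan wording, if such a plan exists), with no new data or patients. The trial gives up any between-group claim on safety or gas exchange, which the design could not support anyway.

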We hypothesize that acute IPF is a manifestation of autoantibody-mediated lung injury, and that mechanistically-focused treatments will have better efficacy than nonspecific, current standard medical therapy. We further anticipate that our rituximab + PEX treatment will result in improved short-term mortality of IPF patients with acute exacerbations, enabling many more of them to survive long enough for definitive lung transplantation. As such, the experimental treatment proposed here will be a beneficial “bridge” to “buy time” for these otherwise doomed patients to benefit from curative lung transplantation.

- 1. **SPECIFIC AIMS**

1. To assess the feasibility and safety of combined PEX, rituximab, and conventional corticosteroid administrations for the treatment of hospitalized patients with acute IPF exacerbations by monitoring indices of respiratory (PaO2) and cardiovascular function during the treatment interval.

2. To assess the efficacy of combined PEX, rituximab, and conventional corticosteroid administrations for the treatment of hospitalized patients with acute IPF exacerbations on patient survival in comparison to historical controls. Patient survival for this investigation will be defined using the composite outcome of 60d survival and/or survival to lung transplantation.

**As such, more IPF patients with acute exacerbations will live long enough to have the clinical evaluations necessary for lung transplantation and until suitable donor organs can be procured.**

We hypothesize the combined treatment will ameliorate autoantibody-mediated lung injury and have a demonstrably beneficial effect on patient outcome.

- 1. **BACKGROUND**

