**2.2.2 Data Collection**

Routine clinical care for seriously ill patients with respiratory insufficiency will be followed as outlined by the primary physician. The study will log the results of monitoring labs consisting of complete blood count (CBC), electrolytes, glucose, BUN, serum creatinine, ionized calcium, magnesium, phosphorus, INR, albumin, liver function tests including of total bilirubin, aspartate alanine transaminase (ALT), and aspartate glutamine transaminase (AST), and complement studies (C3, C4, CH50). These laboratory tests will be logged from the closest available value (+/- 48 hours) on Days 0, 7, 14, 28 or at hospital discharge if < 28 days. In addition to the time points specified above, INR and Ionized calcium will be performed daily during the days when subjects undergoing PEX.

An extra 16 ml of blood needed for T-cell and B-cell studies for research purposes will be drawn at times corresponding to routine blood draws for clinical lab tests. These assays will be carried out in the laboratories of [name].

During hospitalization, subjects will be visited by study personnel within 24 hours after enrollment, and on Days, 7, 14, 28 (or on the day of discharge). A variance of two days will be allowed in the usual follow-up schedule. However, the 24 hour visit and discharge visit should occur on the specified day. In addition, a daily progress note will be made by the treating physician, and placed in the inpatient chart and research subject binder as a source document.

At these visits (Days 0, 7, 14, 28 or at hospital discharge), the following information will be collected and entered into to the study case report forms (CRFs). All clinical and laboratory data are part of routine clinical care and will be collected from medical records.

1. Demographics, physician names and contact information, general medical and surgical histories, co-morbidities, concurrent medications, and allergies.
2. Recording of vital signs and medication regimen.
3. Review of medication changes
4. Brief assessment of symptoms and documentation of any adverse effects.
5. Recording of laboratory and clinical testing results.

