A telephone contact will occur on Day 60 for post treatment survival surveillance. If the subject remains inpatient, the assessment may be completed in the hospital setting. Subjects will be contacted by the study personnel to assess for symptoms potentially related to adverse effects of medications, review of medication changes, and interval medical or surgical histories including emergency or physician office visits. A variance of 3 days will be allowed for the telephone contact to facilitate scheduling or to account for weekends or holidays.

The schedule for patient assessment is outlined as follows (Appendix 2).

Day 0 (Enrollment):

- Informed Consent
- History and physical exam to include vital signs and blood pressure.
- Laboratory evaluations including complete blood count (CBC), electrolytes, glucose, BUN, serum creatinine, calcium, magnesium, phosphorus, albumin, liver function tests, and INR.
- Serology for hepatitis B (HbsAg).
- Assessment of PaO2.
- Complement studies of C3, C4, CH50.
- Assessment of peripheral blood T-cell and B-cell assays .

Day 7:

- Brief history and physical exam to include vital signs and blood pressure.
- Laboratory evaluations including complete blood count (CBC), electrolytes, glucose, BUN, serum creatinine, calcium, magnesium, phosphorus, albumin, liver function tests, and INR.
- Assessment of PaO2.
- Complement studies of C3, C4, CH50.
- Assessment of peripheral blood T-cell and B-cell assays.

Day 14:

- Brief history and physical exam to include vital signs and blood pressure.
- Laboratory evaluations including complete blood count (CBC), electrolytes, glucose, BUN, serum creatinine, calcium, magnesium, phosphorus, albumin, liver function tests, and INR.
- Assessment of PaO2.
- Complement studies of C3, C4, CH50. See above
- Assessment of peripheral blood T-cell and B-cell assays see above

Day 28 (or at hospital discharge if < 28 days):

- Brief history and physical exam to include vital signs and blood pressure.
- Laboratory evaluations including complete blood count (CBC), electrolytes, glucose, BUN, serum creatinine, calcium, magnesium, phosphorus, albumin, liver function tests, and INR.
- Assessment of PaO2.
- Complement studies of C3, C4, CH50.
- Assessment of peripheral blood T-cell and B-cell assays.

Day 60:

- Brief assessment of symptoms and documentation of adverse events, and a review of medical or surgical histories.

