**2.3 STUDY ENDPOINTS**

**2.3.1. The Primary End-Points**

The primary outcome measures for this study are the feasibility and safety of the regimen in patients with IPF exacerbations. Safety will be assessed by monitoring three variables of cardiopulmonary function:

- Respiratory deterioration defined as PaO2 on days 0, 3, 5, 7, 14, 28 (if still hospitalized) while breathing 100% FiO2 for >20 minutes by either endotracheal tube (ETT) or nonrebreathing face mask if not intubated (face masks and O2 delivery systems for nonintubated patients will be standardized).
- Hemodynamic deterioration defined as need for initiation of vasopressor agents, inotropes, or intravenous diuretics.

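### The PaO2 model in Section 2.4.2, read in the ordinary way as a straight line over Days 0–28, can hide and often reverses the sign of an early fall during the exchange and first rituximab days

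*Protocol*

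**What the plan says.** Section 2.3.1 of the protocol sets the status of the endpoint: "The primary outcome measures for this study are the feasibility and safety of the regimen in patients with IPF exacerbations". The respiratory component is "Respiratory deterioration defined as PaO2 on days 0, 3, 5, 7, 14, 28 (if still hospitalized", measured on 100% oxygen. No size of fall is set that would count as deterioration. Aim 1 in Section 1.2 says that safety will be assessed "by monitoring indices of respiratory (PaO2) and cardiovascular function during the treatment interval".

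Section 2.2.1 places plasma exchange on Days 0, 1, 2, 4 and 5, and rituximab on Days 5 and 13.

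Section 2.4.2 gives the analysis: "Mixed effects regression models will be used to assess the treatment effects on gas exchange". The terms are: "Main effects will include treatment, intubation status, time, as well as a treatment by time interaction and random effects for slope and intercept". No visit factor, curve or piecewise term is named. Model assumptions are to be checked, with transformations and then unspecified nonparametric approaches as fallbacks.

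Section 2.2.2 gives a shorter list of visits: "At these visits (Days 0, 7, 14, 28 or at hospital discharge), the following information will be collected". Its visit-by-visit schedule has PaO2 on Days 0, 7 and 14 and at a visit headed "Day 28 (or at hospital discharge if < 28 days". Days 3 and 5 do not appear.

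**The concern.** The aim is about PaO2 while the treatments are being given, and most of that activity falls in Days 0–5. A single slope over 28 days answers a different question: the average trend across the whole stay. The measurement days are also very uneven. Days 3, 5 and 7 all lie before the mean day, so lowering those values tilts a fitted line upward, not downward.

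What is at stake is whether the primary respiratory safety analysis can show a fall that occurs around the exchanges and the first rituximab dose and later resolves. No threshold for deterioration is set that would show it separately. The design is also a single treated group with no control PaO2 data described. The treatment and treatment-by-time terms therefore cannot be estimated, and the time effect is what remains to be interpreted.

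**Working it through.** **Inputs.** The PaO2 days come from Section 2.3.1 (0, 3, 5, 7, 14, 28) and, separately, from Section 2.2.2 (0, 7, 14, 28). The protocol gives no size for a PaO2 fall, so it is written as d and results are multiples of d. The protocol states no figure of its own to reproduce here.

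**Formula.** With complete data, the fixed time slope of a model with random intercept and slope equals the least-squares slope: Σ(t − t̄)y / Sxx, with Sxx = Σ(t − t̄)². Intubation status is left out.

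**Leverage, Section 2.3.1 days.** t̄ = 57/6 = 9.5. The deviations are −9.5, −6.5, −4.5, −2.5, +4.5 and +18.5. Sxx = 90.25 + 42.25 + 20.25 + 6.25 + 20.25 + 342.25 = 521.5. The Day 28 share is 342.25/521.5 = 65.6%.

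**Fitted change over 28 days, subject followed to Day 28** (y = −d on the days of the fall, otherwise 0):

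| Fall of d on | Slope per day | 28-day fitted change | True change, Day 0 to Day 28 |
|---|---|---|---|
| 3, 5; back by 7 | (6.5 + 4.5)d/521.5 = +0.0211d | +0.59d | 0 |
| 3, 5, 7; back by 14 | 13.5d/521.5 = +0.0259d | +0.73d | 0 |
| 3, 5, 7, 14; back by 28 | (13.5 − 4.5)d/521.5 = +0.0173d | +0.48d | 0 |
| 3, 5, 7; half remains on 14 and 28 | (13.5 − 0.5 × 23)d/521.5 = +0.0038d | +0.11d | −0.5d |
| 3 to 28, no recovery | (13.5 − 23)d/521.5 = −0.0182d | −0.51d | −d |
| 14 only | −4.5d/521.5 = −0.0086d | −0.24d | 0 |

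In the second row the fitted Day 0 value is −0.5d − 9.5 × 0.0259d ≈ −0.75d. The line absorbs the fall by starting too low and then rising. For a fall on Days 3–7 the sign turns negative once the share remaining on Days 14 and 28 exceeds 13.5/23 = 59%.

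**Subjects who leave early.**

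- Last value on Day 14 (days 0, 3, 5, 7, 14; t̄ = 5.8, Sxx = 110.8), fall on 3, 5 and 7: (2.8 + 0.8 − 1.2)d/110.8 = +0.022d per day.
- Last value on Day 7 (days 0, 3, 5, 7; t̄ = 3.75, Sxx = 26.75), fall on 3 and 5: (0.75 − 1.25)d/26.75 = −0.019d per day.

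**Section 2.2.2 days (0, 7, 14, 28).** t̄ = 12.25, Sxx = 428.75, and the Day 28 share is 248.06/428.75 = 57.9%. A fall on Day 7 gives 28 × 5.25d/428.75 = +0.34d. A fall on Days 7 and 14 gives +0.23d, and on Day 14 only −0.11d. On this schedule Day 7 is the only early value that could show a fall from the exchange days.

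**Same data, day as a category.** Change from Day 0 for the second profile is −d on Days 3, 5 and 7, and 0 on Days 14 and 28. If d were 50 mmHg (an assumption), this shows a 50 mmHg fall. The straight line shows a rise of 0.725 × 50 ≈ 36 mmHg.

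**The case against.** The strongest reply is that the protocol never says time is linear. A random slope describes how subjects vary around the mean and does not by itself fix the shape of the mean. A categorical day with a random intercept and slope would fit the wording, and the coding of time could be left to an SAP that is not shown. In Section 2.4.2 the word linear is attached to the ventilation-free-days model. This stands in part: straight-line time is an inference. It is still the ordinary reading of one time effect paired with a random slope, and no other form is named.

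A second reply is that assumption checks would expose the misfit. They might, although 10 subjects give little power to see it. No monotone transformation of PaO2 turns a fall and recovery into a line, and the nonparametric fallback is not described.

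A third reply stands in full: the sign depends on timing and length of stay. PaO2 is taken only while the subject is in hospital, and Section 1.3 reports hospital mortality of about 50%. The 66% leverage therefore applies only to those measured on Day 28.

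Two stronger readings are tempting. A reader might infer that a positive slope would be reported as improvement or as proof of safety. The protocol does not say so, and it also tracks haemodynamic deterioration, daily progress notes and safety data as they accrue. A reader might also infer from the Day 28 visit heading that a discharge PaO2 is analysed as if taken on Day 28. That heading only schedules a visit; no text assigns the value to t = 28.

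**Conclusion.** The point holds in a limited form. On its ordinary reading, the only named PaO2 analysis fits Aim 1 badly. For subjects followed to Day 28, an early fall that fully recovers yields a fitted rise of about half to three-quarters of the fall (+0.48d to +0.73d). The slope can be positive even when half the loss remains.

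This rests on time entering as a straight line, complete data for the subject concerned, and no adjustment for intubation status. It needs no variance assumption. It does not show that the model always reverses the sign of harm: a fall on Day 14 only, a largely unrecovered fall, or departure before Day 14 after a fall on Days 3 and 5 gives a negative slope.

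The weight is moderate. It is a cheap improvement to the stated method, not a defect that must be repaired before the trial can be interpreted.

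**What to change.** In Section 2.4.2:

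- State that study day enters the PaO2 model as a categorical factor.
- Report the mean within-subject change from Day 0 on each measured day with a 95% CI. Make the treatment-interval days the main respiratory safety summary: Days 3, 5 and 7, and Day 14 after the Day 13 rituximab.
- List each subject's lowest PaO2 minus the Day 0 value.
- Enter any discharge PaO2 at its actual study day.

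Dropping the random slope is optional.

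Reconcile Section 2.2.2, whose visit lists omit PaO2 on Days 3 and 5, with Section 2.3.1, which lists those days. The day-specific summary depends on this.

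The cost is protocol or SAP wording. The downside is somewhat wider day-specific intervals than a single slope would have.
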